# Gabapentin as add-on to morphine for severe neuropathic or mixed pain in children from age 3 months to 18 years - evaluation of the safety, pharmacokinetics, and efficacy of a new gabapentin liquid formulation: study protocol for a randomized controlled trial

**DOI:** 10.1186/s13063-018-3169-3

**Published:** 2019-01-15

**Keywords:** Gabapentin, Neuropathic pain, Children, Pharmacokinetics

## Abstract

**Background:**

Gabapentin has shown efficacy in the treatment of chronic neuropathic or mixed pain in adults. Although pediatric pain specialists have extensive experience with gabapentin for the treatment of neuropathic pain, its use is off-label. Its efficacy and safety in this context have never been shown. The aim of this trial is to compare gabapentin with placebo as add-on to morphine for the treatment of severe chronic mixed or neuropathic pain in children. This trial is part of the European Union Seventh Framework Programme project Gabapentin in Paediatric Pain (GAPP) to develop a pediatric use marketing authorization for a new gabapentin suspension.

**Methods/design:**

The GAPP-2 study is a randomized, double-blind, placebo-controlled, multicenter superiority phase II study in children with severe chronic neuropathic or mixed pain. Its primary objective is to evaluate the efficacy of a gabapentin liquid formulation as adjunctive therapy to morphine. Sixty-six eligible children 3 months to 18 years of age with severe pain (pain scores ≥ 7), stratified in three age groups, will be randomized to receive gabapentin (to an accumulating dose of 45 to 63 mg/kg/day, dependent on age) or placebo, both in addition to morphine, for 12 weeks. Randomization will be preceded by a short washout period, and treatment will be initiated by a titration period of 3 weeks. After the treatment period, medication will be tapered during 4 weeks. The primary endpoint is the average pain scores in the two treatment groups (average of two measures each day for 3 days before the end-of-study visit [V10] assessed by age-appropriate pain scales (Face, Legs, Activity, Cry, Consolability scale; Faces Pain Scale–Revised; Numeric Rating Scale). Secondary outcomes include percentage responders to treatment (subjects with 30% reduction in pain scale), number of episodes of breakthrough pain, number of rescue interventions, number of pain-free days, participant dropouts, quality of life (Pediatric Quality of Life Inventory), and acceptability of treatment. Outcomes will be measured at the end-of-study visit after 12 weeks of treatment at the optimal gabapentin dose. Groups will be compared on an intention-to-treat basis.

**Discussion:**

We hope to provide evidence that the combination of morphine and gabapentin will provide better analgesia than morphine alone and will be safe. We also aim to obtain confirmation of the recommended pediatric dose.

**Trial registration:**

EudractCT, 2014-004897-40. Registered on 7 September 2017.

ClinicalTrials.gov, NCT03275012. Registered on 7 September 2017.

**Electronic supplementary material:**

The online version of this article (10.1186/s13063-018-3169-3) contains supplementary material, which is available to authorized users.

## Background

Chronic pain, continuous or recurrent, lasting for more than 3 months affects 11–35% of children with varying disabilities [1, 2]. Although nonsteroidal anti-inflammatory drugs and opioids may be the standard therapy for mild and severe non-neuropathic pain (non-NP) in both adults and children, and although tramadol and morphine have shown efficacy in different types of NP in adults [3–5], they are not considered to be the first-line medications for NP syndromes [6–8], owing to concerns regarding long-term safety. Nevertheless, opioids are used for patients with severe NP not responding to first-line medications in acute NP or episodic exacerbation of severe NP. Because of a lack of appropriate studies in children concerning management of chronic NP, the latter are often undertreated or pain medication is used off-label.

The antiepileptic drug gabapentin has shown efficacy in a wide range of neuropathic or mixed pain syndromes. The mechanism of gabapentin is at the voltage-activated calcium channels in the central nervous system (CNS), but the mode of action in the treatment of NP is still not fully understood. In early studies, gabapentin has been shown to have a central antiallodynic effect [9] as well as to inhibit ectopic discharge activity from injured peripheral nerves [10]. Although originally the hypothesis was that it exerted its antiallodynic effect through γ-aminobutyric acid-mediated pathways at the spinal cord and brain level or by antagonism of *N*-methyl-d-aspartate receptors, evidence is emerging for antagonism of calcium channels in the CNS and peripheral nerves [9, 11]. Fink et al. showed that gabapentin in the neocortex of the rat but also in humans inhibits neuronal calcium influx, leading to decreased α-amino-3-hydroxy-5-methyl-4-isoxazole propionic acid receptor activation and noradrenaline release in the brain [12]. More recently, it was suggested that gabapentin also inhibits activation of a nuclear transcription factor and consequently expression of cyclooxygenase 2 and other genes involved in inflammation [13].

In adults, randomized controlled trials of gabapentin have shown its efficacy and safety for the treatment of postherpetic neuralgia [14, 15], diabetic neuropathy [16], phantom limb pain [17], spinal cord injury [18], peripheral nerve injury [19], and neuropathic cancer pain [20]. Case series and case reports further suggest its efficacy for analgesia in multiple sclerosis [21, 22], complex regional pain syndrome type 1, erythromelalgia, trigeminal neuralgia, peripheral neuropathy, post-thoracotomy neuropathy, central pain syndromes, and Guillain-Barré syndrome [23].

Efficacy in pediatric pain is based mainly on anecdotal reports and several open-label, noncontrolled clinical studies. Gabapentin appears efficacious for the treatment of post-thoracotomy pain, complex regional pain syndrome type 1, phantom limb pain, and spinal fusion surgery [24–26].

Hence, although pediatric pain specialists have extensive experience with the use of gabapentin and reports support its benefits, efficacy and safety have not been unequivocally demonstrated in well-designed clinical efficacy and safety studies in the pediatric population.

In this context, the GAPP (Gabapentin in Paediatric Pain) project is a European-funded project that comprises a full pediatric development program for gabapentin in the treatment of chronic neuropathic or mixed pain in children. The development strategy, requirements, and regulatory deliverables have been outlined in a pediatric investigation plan (PIP), which has agreed with and approved by the European Medicines Agency’s Paediatric Committee.

The PIP includes (1) the development of a liquid oral gabapentin formulation, (2) the evaluation of gabapentin safety in juvenile animal toxicity studies (PRE-GABA), (3) two clinical trials to evaluate the efficacy and safety of gabapentin as monotherapy (GABA-1) and as adjuvant therapy (GABA-2), and (4) a modeling bridging study (GABA-3) to specifically address the paucity of pharmacokinetic (PK) data in children and enhance the dose rationale for the pediatric population [27]. The study protocol presented in this paper concerns the GABA-2 trial. The primary aim of this specific study (GABA-2) is to determine the efficacy and safety of gabapentin versus placebo as add-on to morphine in children with severe chronic neuropathic or mixed pain.

## Methods/design

In this randomized, double-blind, placebo controlled, multicenter superiority phase II study, the efficacy of gabapentin as add-on to morphine will be compared with the efficacy and safety of placebo as add-on to morphine.

### Study population

A total of 66 children from 3 months to 18 years of age with chronic (> 3 months) neuropathic or mixed (neuropathic and nociceptive component) pain are being recruited into the trial. Subjects are recruited in several centers for pediatric pain divided over six European Union countries (Table 1).

**Table 1 Tab1:** List of recruiting centers participating in the GABA-2 clinical trial

Albania	Qendra Spitalore Universitare Nene Tereza General Pediatric Clinic - Pediatric Department [name], Albania Principal Investigator: [name]
France	Assistance Publique Hôpitaux de Paris - APHP Hôpital Robert Debré Centre of Clinical Investigations, INSERM CIC1426 [name], France Principal Investigator (Country Coordinator): [name] Centre d’évaluation et de traitement de la douleur Co-investigator: [name]
	Assistance Publique Hôpitaux de Paris - APHP Hôpital Necker Centre d’évaluation et de traitement de la douleur [name], France Principal Investigator: [name]
	Hôpital d’enfants Armand Trousseau* Centre de Référence de la migraine de l’enfant et de l’adolescent et du Centre de la douleur [name] Sub-Investigator: [name]
	Assistance Publique Hôpitaux de Marseille - APHM Hôpital La Timone Service de Pédiatrie [name], France Principal Investigator: [name]
	Centre Hospitalier Régional Universitaire de Lille - CHRU Lille Hôpital Roger Salengro Service de Neuropédiatrie - Consultation Douleur Enfant [name], France Principal Investigator: [name]
Germany	Universitaetsklinikum Erlangen Department of Paediatrics and Adolescent Medicine [name], Germany Principal Investigator: [name]
Greece	Geniko Nosokomeio Paidon I Agia Sofia Anaesthetic department & Pain Clinic [name], Greece Principal Investigator: [name]
Italy	Azienda Ospedaliero - Universitaria Consorziale Policlinico di Bari U.O.C. di Neuropsichiatria Infantile [name], Italy Principal Investigator (Country Coordinator): [name]
	Azienda Ospedaliera di Padova Department of Women and Child Health [name], Italy Principal Investigator: [name]

#### Inclusion criteria

Subjects must fulfill the following inclusion criteria to be eligible:Children aged 3 months to 18 yearsDiagnosis of neuropathic or mixed pain

Because there are no validated tools for the diagnosis of NP in children, diagnosis will be based on Treede et al. criteria [28]:Pain with a distinct neuroanatomically plausible distributionMedical history suggestive of a relevant lesion or disease affecting peripheral or central somatosensory systemClinical examination with demonstration of a distinct neuroanatomical distribution by at least one confirmatory testDiagnostic test confirming lesion or underlying disease (e.g., magnetic resonance imaging or computed tomographic scan or laboratory test confirming metabolic disease)

Patients must at least meet one of four mentioned criteria if younger than 3 years old and at least two of four criteria if older than 3 years of age [28].

For complex regional pain syndrome, the so-called Budapest criteria will be used for the diagnosis [29]. This means there is continuing pain disproportionate to the inciting event.

Patient must report at least one symptom in three of four of the following categories:Sensory: allodynia and/or hyperalgesiaVasomotor: temperature asymmetry, skin color changes/asymmetryPseudomotor/edema: edema and/or sweatingMotor/trophic: motor dysfunction and/or trophic changes (nail/skin)

This together with at least one sign during evaluation in two or more of the previous categories and no other diagnosis can explain the symptoms.3.Severe pain

Severe pain is defined as intensity 7 or more assessed during a 3-day screening period using the following scores according to age: Face, Legs, Activity, Cry, Consolability scale (FLACC) for children ages 3 months up to and including 2 years; Faces Pain Scale–Revised (FPS-R) for children aged 3 years up to and including 7 years; and the pain Numeric Rating Scale (NRS-11) for children between 8 and 18 years old. Pain intensity is assessed two times daily and at least five of six assessments should be available.4.There should be chronic or recurrent pain for a period of at least 3 months.5.Informed consent from parents or legal guardian6.A stable underlying disease condition and treatment7.Patients with chemotherapy-induced peripheral neuropathy when in clinical remission or maintenance phase of their therapeutic protocol

#### Exclusion criteria

Pain duration of more than 5 yearsCurrent use of gabapentinCurrent use of strong opioids (morphine, methadone, fentanyl, oxycodone) or ketamineHistory of failure to respond to treatment with gabapentin or opioids for NPHistory of epilepsy (except febrile seizure)Subjects diagnosed with sickle cell diseaseSubjects diagnosed with cognitive impairmentSubjects who present with current controlled or uncontrolled comorbid psychiatric diagnosis that can impair pain diagnosis and assessmentSubjects with a history of or current suicidal ideation or behaviorSubjects with a history of substance abuse in particular opioidsSubjects being treated with prohibited concomitant medication (*see* Table 2)Subjects with a body mass index below the 5th percentile or above the 95th percentile for their age and genderSubjects with renal impairment (i.e., glomerular filtration rate < 90 ml/min/1.73 m^2^)Subjects with hepatic impairment (aspartate transaminase/aAlanine transaminase three times the upper limit of normal for age)Corticosteroid oral treatment or infiltration needed for pain caused by infiltration or compression of neural structuresSubjects with clinically relevant abnormal electrocardiogram (ECG) at the screening visitSubjects with a known allergy/hypersensibility/significant intolerance to any component of the study drugsSubjects with fructose intolerance, diabetes, glucose-galactose malabsorption, or lactase-isomaltase deficiencySubjects participating in another clinical trialSubjects scheduled for surgery or in recovery from surgery within 3 months of baseline assessmentFemale subjects who are pregnant or lactatingSubjects who fail screening or were previously enrolled in this studyPatients with chemotherapy-induced peripheral neuropathy when in induction phase of their therapeutic protocol

**Table 2 Tab2:** Prohibited concomitant medication

- Tricyclic antidepressants, selective serotonin reuptake inhibitors, selective noradrenalin reuptake inhibitors, antipsychotics, neuroleptics, anxiolytics, benzodiazepines, psychostimulants, mono amine oxidase inhibitors, sedatives	
- Anticonvulsant medications as pregabalin, valproic acid, etc.	
- All NSAIDs with exception of ibuprofen	
- Opioids	
- Benzodiazepines	
- Ketamine	
- Lidocaine	
- Medical cannabis	

*NSAIDs* Nonsteroidal anti-inflammatory drugs

### Screening, assessment, and randomization

#### Screening period

After obtaining informed consent from the subjects’ parents or legal representatives, during a screening period to confirm study eligibility, a medical history, including all relevant lifetime medication and nonpharmacological interventions, will be obtained, and concomitant medication will be recorded. Also, required clinical laboratory tests will be done. Venous blood samples will be taken for standard clinical hematology and biochemistry (2.5 ml) together with a serum β-human chorionic gonadotropin test (in females of childbearing age) (2 ml) and a sample for pharmacogenomics (0.5 ml) and metabolomics (1 ml).

A washout period of 3 days may be required to discontinue medication potentially interfering with the primary outcome of pain intensity, with the exception of the rescue medications paracetamol and ibuprofen.

#### Baseline assessment

After the washout period, the patient and, dependent on the age of the child, the child’s parents will be requested to assess pain intensity twice daily for 3 days to obtain the average baseline pain intensity. During this period, rescue medication will be allowed (i.e., paracetamol 15 mg/kg [oral or rectal] four to six times daily to a maximum daily dose of 4 g or ibuprofen 5–10 mg/kg [oral] every 6–8 h to a maximum daily dose of 30 mg/kg/day).

#### Randomization

After the screening period, the patients return to the trial center and will be randomized (on V2) at a 1:1 ratio to one of the treatment groups: gabapentin plus morphine or placebo plus morphine.

Randomization is performed using ICE version 1.0 software and generated by a statistician not involved in data analysis of trial results. After randomization login, a blinded message is sent to the investigator, and an unblinded message is sent to the pharmacy.

Patients are stratified into three age groups (3 months to 3 years, 3 years to 8 years, and 8 years to 18 years) with pain scores validated for that age group.

### Treatment period

#### Dose and dose optimization

During the first 3 weeks of treatment period 4 (V3–V6 in the participant timeline) (Fig. 1), visits will be scheduled to assess safety and tolerability and to titrate liquid gabapentin (75 mg/ml) to an optimal, weight-based (two weight groups, 5 to ≤ 15 kg and > 15 kg) tolerable dosage. A dose will be indicated as optimal if the subject has reached a pain intensity < 4/10 in all pain assessments in the last 48 h (*n* = 4) or the maximum tolerable dose. Only one dose reduction is allowed during the optimization period (Table 3).

**Fig. 1 Fig1:**
[figure not shown]
Participant timeline

**Table 3 Tab3:** Dose optimization schedule of gabapentin

Weight group	V2	V3	V4	V5	V6
5–15 kg	7 mg/kg/day corresponding to 0,09 ml/kg/day	14 mg/kg/day corresponding to 0,19 ml/kg/day	21 mg/kg/day corresponding to 0,28 ml/kg/day	42 mg/kg/day corresponding to 0,56 ml/kg/day	63 mg/kg/day corresponding to 0,84 ml/kg/day
> 15 kg	5 mg/kg/day corresponding to 0,07 ml/kg/day	10 mg/kg/day corresponding to 0,13 ml/kg/day	15 mg/kg/day corresponding to 0,2 ml/kg/day	30 mg/kg/day corresponding to 0,4 ml/kg/day	45 mg/kg/day corresponding to 0,6 ml/kg/day

All children will have a titration in morphine starting at 0.6 mg/kg/day to a maximum dose of 1.2 mg/kg/day four times daily from days 1 to 5, based on the World Health Organization (WHO) guidelines of 2012 [30]. For patients with a body weight of 30 kg or less, a liquid formulation will be used during titration and maintenance phases. For patients with a body weight of 30 kg or more, a solid immediate release formulation will be used during titration phase, which will be converted to a similar daily dose solid extended release formulation during maintenance phase. During all visits in the dose optimization and maintenance period, adverse effects of morphine will be closely monitored (e.g., constipation, for which laxatives can be given).

At dose optimization visit V5 or V6 (or at end-of-study [EOS] visit V10), four venous blood samples will be taken for assessment of PK: One predosing and three at different times postdosing (four times 1.5 ml and for children less than 15 kg four times 1 ml).

#### Fixed-dose maintenance period

After dose optimization, patients will continue to take medication (gabapentin or placebo) next to morphine for an additional 12 weeks. Dose adjustments are not allowed during the maintenance period.

### End of study

For all patients who terminate or complete the dose maintenance period, medication will be tapered according to a schedule over 0–4 weeks. During this tapering period, site staff will contact the patients to ensure that they are complying with the taper schedule. At EOS visit V10, venous blood sampling will be done once again (standard clinical hematology and biochemistry [2.5 ml] and metabolomics [1 ml]).

### Study taper and follow-up period

#### End of taper

All patients who are tapered off medication will return for a visit 1–4 weeks after their EOS visit for the collection of final safety evaluations.

#### Follow-up

Seven days after the last dose of investigational medication, follow-up by phone will take place to collect information about pain intensity, global health, and ongoing or new (serious) adverse events and concomitant medication until all safety concerns are resolved.

#### Blinding

Gabapentin and placebo (oral liquid formulation) will be indistinguishable in appearance to maintain the study blinding. Also, labeling will not allow recognition of actual treatment. During the trial, blinding will be broken by the investigator for emergency purposes only, where knowledge of the blinded treatment could influence further patient care. In addition, the safety contact will unblind safety reports, as per regulatory requirements. Study blinding will be broken after database lock.

#### Efficacy measurement

The following scales will be used to assess pain intensity at all visits throughout the study. The FLACC scale is used for children between 3 months and 7 years of age who are unable to self-report their pain. It is a five-item scale that raters (investigators, parents) use to score in five categories (Face, Legs, Activity, Cry, and Consolability), each assigned a score of 0, 1, or 2 and total score between 0 and 10.

The FPS-R is a self-report measure of pain intensity. It consists of six line drawings of faces that are scored 0 to 10. In this study, the FPS-R will be used for assessment of pain in children 3 years and older because it has not been validated for younger children. In children of 3 and 4 years old who are unable to self-report using the FPS-R, the FLACC scale will be used.

The Numeric Rating Scale (NRS-11) is designed for pain score to be used by children from 8 years of age. The user has the option to verbally rate their scale from 0 to 10 or to place a mark on a line indicating their level of pain, with 0 meaning absence of pain and 10 meaning the most intense pain possible.

To be able to compare data from the different pain scores, all scores will be reported on a scale of 0–10, as indicated by the individual scores.

Pain will be assessed at the following time points:Baseline assessment: average pain score of twice-daily assessment on 3 consecutive daysDuring trial: daily in the morning and when breakthrough pain is noticedEndpoint: average pain score of twice-daily assessments on 3 consecutive days

Furthermore, parents and/or subjects are asked to keep a daily patient diary recording the following items: study drug intake changes, comedication intake including rescue medication, adverse events, and abnormalities in sleep.

Additionally, the following items will be scored:Global satisfaction with treatment (at EOS visit V10) using NRS-11Clinical Global Impressions Scale (CGI-EI [Investigator]) at V2, V6, and EOS V10Patient Global Impression of Change (PGIC) Scale at V6 and EOS V10Pediatric Quality of Life Inventory (PedsQL) Generic Core ScaleFive Point Facial Hedonic Scale at EOS V10 for acceptability of the oral suspensionAdverse events collectionColumbia Suicide Severity Rating Scale (C-SSRS) at V1 and EOS V10Modified Overt Aggression Scale at V2, V6, and EOS V10

#### Outcome measurements

The primary outcome of the study is the average pain score (defined as average pain score of twice-daily assessments of 3 consecutive days) at the end of the study period in both treatment groups. Secondary endpoints are percentage of responders with 30% reduction in pain score, average daily pain intensity by age-appropriate scale, observational pain assessment with use of NRS-11 by parents/caregivers and investigator at each visit, number of episodes of breakthrough pain > 4/10 pain score and use of rescue medication, number of rescue interventions, number of pain-free days with < 4/10 pain score without rescue medication, participant dropouts due to lack of efficacy, total cumulative weight dose of each rescue drug, quality of life scored with the PedsQL at baseline (V2) and EOS visit (V10), acceptability of treatment (Facial Hedonic Scale) at EOS visit, global satisfaction with treatment (NRS-11 completed by parent/patient) at EOS visit, CGI-S at V6 and EOS (CGI-S by investigator), patient/parent PGIC at V6 and EOS, PK parameters: apparent clearance (CL/F), apparent volume of distribution (Vd/F), absorption rate constant (Ka), area under the curve (AUC), maximum (peak) concentration (Cmax), time of maximum concentration (Tmax), concentration at steady-state (Css), minimum concentration (Cmin) incidence of adverse events, percentage of adverse events, percentage of subjects discontinuing the trial due to adverse events, aggressive behavior in children > 6 years old (Retrospective-Modified Overt Aggression Scale) at V2–V6 and EOS, and suicidal ideation (C-SSRS) at V1 and EOS.

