### Statistical analysis

#### Sample size calculation

A total sample size of 66 is needed. It will allow detection of a significant difference between morphine plus placebo and morphine plus gabapentin groups in mean pain scores at EOS. Mean baseline pain scores of 8.5 are assumed for both groups, with estimated EOS pain scores of 5.4 for morphine alone versus 4.5 for morphine plus gabapentin based on percentage change in pain scores in a previous trial in adults [31].

A minimum number of patients is defined per age group: (1) at least 5 patients aged 3 months to less than 3 years, (2) at least 15 patients aged 3 years to less than 7 years, and (3) at least 20 patients aged 7 years to less than 18 years. No maximum number of patients per age group is specified. A two-tailed test will be applied with a significance level of 0.5 and a power of 80%, and 10% dropout is anticipated.

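### Suicidal ideation is a secondary endpoint with only one scheduled post-baseline rating, about 15 weeks after first dose, and none at V6 or at the end-of-taper visit

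*Protocol article*

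**What the plan says.** The section Outcome measurements names "suicidal ideation (C-SSRS) at V1 and EOS" as a secondary endpoint. The assessment list under Efficacy measurement gives the same two time points and identifies EOS as V10. The same list places the aggression scale and the investigator's global impression at V2, V6 and V10, and the patient's global impression of change at V6 and V10.

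The Exclusion criteria rule out any child with past or current suicidal ideation or behaviour.

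On timing, the abstract says that "treatment will be initiated by a titration period of 3 weeks", and maintenance then runs "for an additional 12 weeks" (Fixed-dose maintenance period). Under End of study, the introduction to the taper reads "For all patients who terminate or complete the dose maintenance period", and then "medication will be tapered according to a schedule over 0–4 weeks". Under End of taper, the children being tapered "will return for a visit 1–4 weeks after their EOS visit for the collection of final safety evaluations". A telephone follow-up takes place seven days after the last dose. The C-SSRS is named at neither contact.

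**The concern.** An endpoint on emergent ideation needs ratings when ideation could emerge. Here the first rating is made before randomisation in children already selected to be free of ideation, so it carries almost no information on emergence. Everything rests on the second rating, at the end of maintenance. The whole of dose optimisation, and the change from optimisation to a fixed dose, lie between the two ratings. The taper lies after both.

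Two things are at stake. The first is completeness: an episode that begins and resolves before V10, or begins during the taper, may not be recorded by the instrument chosen for this endpoint. The second is oversight. The data and safety monitoring committee evaluates safety continuously, but systematic ratings would reach it only as each child arrives at V10.

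The schedule also treats two behavioural safety measures differently without giving a reason: aggression has a rating at V6 and suicidality does not.

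**Working it through.** The plan gives no figure of its own for this endpoint, so there is none to reproduce. The check is arithmetic on the visit schedule.

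**Time from first dose to the only post-baseline rating**
- Dose optimisation: 3 weeks (abstract; Dose and dose optimization). The first dose step is at V2 (Table 3).
- Maintenance: 12 further weeks (Fixed-dose maintenance period).
- 3 + 12 = 15 weeks; 15 × 7 = 105 days.
- The interval from V1 is somewhat longer, because the baseline pain assessment and any washout precede V2.

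**Time after that rating**
- Taper: 0 to 4 weeks (End of study).
- From first dose to end of taper: 15 + 0 = 15 to 15 + 4 = 19 weeks. No rating is named in the last 0 to 4 of them.

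**Scheduled ratings, side by side**

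| Measure | Before treatment | V6 | V10 | End of taper |
|---|---|---|---|---|
| C-SSRS | V1 | no | yes | not named |
| Aggression scale | V2 | yes | yes | not named |
| Global impression (investigator) | V2 | yes | yes | not named |
| Global impression of change (patient) | none | yes | yes | not named |

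**Children who might have no post-baseline rating**
- Inputs: "A total sample size of 66 is needed" and "10% dropout is anticipated" (Sample size calculation).
- 66 × 0.10 = 6.6, so about 7 children leave early. How many of them stop during dose optimisation is not given, so the range is 0 to about 7.
- Not every child can be rated, since enrolment starts at 3 months. The article gives no age limit for the C-SSRS. Assume that ratable children are roughly the oldest age group in the sample size section, 7 years and above.
- The age-group minimums are 5, 15 and 20. The oldest group therefore holds at least 20 children and at most 66 − 5 − 15 = 46.
- 10% of 20 = 2.0 and 10% of 46 = 4.6. Under this assumption at most about 5 ratable children leave early, and those who stop during dose optimisation are an unknown subset that may be zero.

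**The case against.** The strongest reply is that nothing here is wrong or contradictory. The two lists agree, and a screening rating that supports an exclusion, followed by a rating at the end of treatment, is a coherent minimum for an exploratory trial. That stands: this is a weakness in how the endpoint is measured, not an inconsistency.

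Stronger readings are tempting, and the document does not support them.

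- *Treatment goes unrated for 15 weeks.* V10 is itself an on-treatment rating for completers. The gap lies between V1 and V10.
- *Ideation that comes and goes before V10 is lost.* This depends on the recall window, which the article does not state. If the V10 form asks about the time since the previous visit at which the scale was completed, it covers the interval in principle, though it relies on a child's or parent's recall over 15 weeks. If it asks about the present or a short window, it does not cover the interval.
- *Early stoppers are never rated, so the incidence is biased downward.* The End of study text includes children who terminate maintenance early, and End of taper speaks of an EOS visit for all tapered children. Only stopping during dose optimisation is unclear. The procedures figure, which is not shown, or the full protocol may settle it.
- *Seven of 66 children have missing data.* That is a ceiling: it assumes that every dropout lacks an EOS visit and that every child can be rated.

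It is also true that adverse events are collected throughout, through the diary, the end-of-taper visit and the follow-up call, so ideation that is volunteered can be recorded. Spontaneous reporting does not replace the structured rating chosen for this endpoint, however, and the absence of a V6 and an end-of-taper rating stands on the article's own text. It is not a detail left to another document, because the article fixes the time points twice.

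**Conclusion.** The point holds as a cheap improvement. The schedule gives one post-baseline C-SSRS rating per child, about 105 days after first dose, with none during or at the end of dose optimisation and none named in the 0 to 4 weeks of taper. Systematic ratings cannot inform the monitoring committee before a child's V10.

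How many episodes this would miss cannot be stated: the article gives no expected rate of ideation and no recall window. A downward bias is possible if affected children leave unrated, but it is not shown. The number of children who stop during dose optimisation without a rating lies between 0 and about 7 of 66, or at most about 5 if only children of about 7 years or older can be rated. The first range rests on the anticipated 10% dropout; the second adds the age assumption. The primary analysis is not affected.

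**What to change.** For children old enough to be rated:

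1. Complete the C-SSRS at V6 and at the existing end-of-taper visit, in addition to V1 and V10.
2. Complete it at the last visit of any child who stops early, and say explicitly that this includes stopping during dose optimisation.
3. Use a since-last-visit recall period for every post-baseline rating, and state it.
4. Report any post-baseline ideation by arm, with the number of children rated as the denominator.

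The cost is a few minutes per visit and one changed line in the schedule. No visit is added and no dose or clinical rule changes. At two extra forms per child, and under the age assumption used above, that is between 20 × 2 = 40 and 46 × 2 = 92 extra forms over the whole trial. The Trial status section says that no patients had yet been included, so at that point every child could have been rated on the fuller schedule.
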